### Secondary outcomes

Metabolic and anthropometric parameters: blood glucose, lipids, blood pressure, BMI, waist-to-hip ratio, HOMA-IR, body composition analysis, Vitamin D.Vascular and cardiac assessments: peripheral vascular status, myocardial status (left ventricular thickness, interventricular septum thickness), cardiovascular risk assessment indices (China-PAR score, Framingham Risk Score, QRISK3 score).TCM symptom score and quality of life scores.

### Safety assessment

1.Safety evaluation indicators

Safety evaluation indicators include physical examination, vital signs (heart rate, respiration, temperature, blood pressure), laboratory tests, and adverse events (AEs), including severe adverse events (SAEs). Laboratory tests include complete blood count, urinalysis, blood biochemistry, and 12-lead ECG. Blood biochemistry will specifically include alanine aminotransferase (ALT), aspartate aminotransferase (AST), albumin (ALB), creatinine (Cr), blood urea nitrogen (BUN), and estimated glomerular filtration rate (eGFR).

During the treatment period, investigators must carefully observe and record all AEs and unexpected toxic side effects (including symptoms, signs, and laboratory abnormalities). Regardless of whether an AE is considered related to the investigational product, it must be documented in detail in the case report form (CRF), including time of onset, symptoms, signs, severity, duration, laboratory values, treatment administered and outcome, time elapsed, and follow-up time.
2.Clinical Events Committee and Independent Data Monitoring CommitteeA Clinical Events Committee (CEC) comprising a cardiologist, a neurologist, and an imaging specialist has been established. The CEC will adjudicate all suspected cardiovascular and cerebrovascular endpoints (including 3P-MACE) and all serious adverse events (SAEs) in a blinded manner using pre-defined diagnostic criteria.

An Independent Data Monitoring Committee (IDMC) composed of a cardiovascular specialist, a neurologist, and a biostatistician has also been established. The IDMC is independent of the sponsor and investigators.
3.Pre-specified SAEs related to TJC componentsIn consideration of the Hirudo (Shuizhi) component, the following events are pre-specified as SAEs requiring immediate reporting and adjudication:① bleeding requiring platelet transfusion or hospitalization; intracranial hemorrhage; gastrointestinal bleeding requiring transfusion; clinically significant mucosal bleeding requiring medical intervention; ② prolongation of APTT or PT > 1.5× upper limit of normal (ULN); platelet count < 50 × 10⁹/L; ③ ALT or AST elevation > 3× ULN; eGFR reduction > 30% from baseline or < 45 mL/min/1.73 m^2^; serum creatinine doubling from baseline.
4.Blinded interim safety reviewA pre-specified blinded interim safety review will be conducted when 265 participants (50% of the planned sample) have completed 12 weeks of treatment. The IDMC will review the incidence of SAEs that are possibly, probably, or definitely related to the investigational product, without being unblinded to treatment assignment. If the pooled incidence of drug-related SAEs exceeds a pre-defined safety threshold (based on historical data of TJC and similar herbal products), the IDMC may request unblinding of group assignments to assess whether the signal is disproportionate. The IDMC may then recommend early trial termination, protocol modification, or continuation. All recommendations will be documented and submitted to the ethics committee.
5.Emergency unblinding procedureIf a serious adverse event (particularly bleeding) requires knowledge of treatment allocation for clinical management, the investigator may request emergency unblinding through the trial coordinating center. Upon verification, the investigator will be informed of the patient's group assignment within 4 h. The reason, date, and outcome will be recorded in the CRF and reported to the IRB and IDMC within 24 h. All SAEs will be followed until resolution or stabilization.

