### Inclusion criteria

Age ≥65 years.Meets the diagnostic criteria for MetS.Meets the pattern diagnosis criteria for Qi deficiency and blood stasis.High cardiovascular and cerebrovascular risk population, meeting any one of the following criteria (35):
4.1.History of myocardial infarction.4.2.History of stroke or transient ischemic attack.4.3.History of coronary, carotid, or peripheral arterial revascularization.4.4.Coronary, carotid, or lower extremity arterial stenosis >50%.4.5.Positive exercise stress test or documented symptomatic coronary artery disease by any cardiac imaging, or unstable angina with ECG changes.4.6.Chronic heart failure (NYHA class II-III).4.7.Chronic kidney disease (eGFR <60 mL/min/1.73m^2^).

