### Exclusion criteria

Secondary dyslipidemia, hypertension, or hyperglycemia.Type 1 diabetes mellitus.History of allergy to the study drugs.Acute coronary or cerebrovascular event within the past 14 days.Planned coronary, carotid, or peripheral arterial revascularization.Chronic heart failure (NYHA class IV).Undergoing continuous renal replacement therapy.End-stage liver disease.History of solid organ transplantation or on waiting list for solid organ transplantation.Malignancy.

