**Data collection**					
Written informed consent	□				
Inclusion/exclusion criteria	□				
Demographics	□				
Obtain central random number	□				
Previous history, medical history, and allergies	□				
Comorbidities and co-medications	□	□	□	□	□
Safety evaluation					
Vital signs and physical examination	□	□	□	□	□
Blood routine, Urine routine, Fecal routine	□		□	□	
Liver function(ALT, AST, ALB), kidney function(UN, Cr, UA, eGFR)	□		□	□	
12-Lead ECG	□		□	□	□
Efficiency evaluation					
Composite outcome measures	□	□	□	□	□
Preset exploration indicators	□	□	□	□	□
BMI, waist to hip ratio, body fat analysis	□	□	□	□	□
Blood glucose, blood lipids, blood pressure	□		□	□	□
Fasting insulin, C-peptide, HOMA-IR	□		□	□	□
Cardiovascular and cerebrovascular risk index	□		□	□	□
Troponin, cardiac enzymes, BNP	□		□	□	□
Vitamin D	□			□	□
UACR	□		□	□	□
Cardiac color doppler ultrasound	□			□	□
Neck vascular ultrasound	□			□	□
Traditional chinese medicine syndrome points	□	□	□	□	□
Quality of life rating	□	□	□	□	□
Omics analysis	□			□	

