### Pre-specified exploratory outcomes

Composite cardiovascular outcome (cardiovascular death, non-fatal MI, non-fatal stroke, coronary revascularization, or hospitalization for unstable angina or heart failure).All-cause mortality.Renal and glucose-related retinal microvascular composite outcomes.
3.1.Renal composite outcome: New-onset persistent macroalbuminuria (UACR >300 mg/g), or persistent doubling of serum creatinine from upper limit of normal or eGFR <45 mL/min/1.73m^2^, or requiring continuous renal replacement therapy or death due to renal disease.3.2.Diabetic retinopathy microvascular composite outcome: Requiring retinal photocoagulation or intravitreal injections, vitreous hemorrhage, or blindness.

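### eGFR below 45 counts as a renal outcome and as a pre-specified SAE with no baseline condition, although patients may be enrolled already below 45

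*Protocol article*

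**What the plan says.** **Eligibility.** Under Inclusion criteria, item 4, a patient is high risk when "meeting any one of the following criteria" holds. Item 4.7 is "Chronic kidney disease (eGFR <60 mL/min/1.73m^2", with no lower bound, so a low eGFR alone meets the high-risk requirement. In the Exclusion criteria the only entry based on kidney function is "Undergoing continuous renal replacement therapy".

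**Renal outcome.** Pre-specified exploratory outcomes, item 3.1, opens with "New-onset persistent macroalbuminuria (UACR >300 mg/g" and continues with "persistent doubling of serum creatinine from upper limit of normal or eGFR <45 mL/min/1.73m^2", followed by renal replacement therapy or renal death.

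**SAE list.** Safety assessment, item 3, says that "the following events are pre-specified as SAEs requiring immediate reporting and adjudication". The renal entries are "eGFR reduction > 30% from baseline or < 45 mL/min/1.73 m^2^; serum creatinine doubling from baseline".

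**Schedule.** In Table 1 the row "Liver function(ALT, AST, ALB), kidney function(UN, Cr, UA, eGFR" is marked at baseline, week 12 and week 26, but not at week 52. Blood glucose, lipids and UACR are marked at week 52. Recording of adverse events starts at Visit 2.

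**The concern.** Both event definitions use an absolute level of eGFR in a trial whose entry rule admits patients already below that level. Of the renal SAE entries, the 30% fall and the creatinine doubling are stated relative to baseline; the limit of 45 is not. In the renal composite the new-onset qualifier is attached to macroalbuminuria only.

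Read as written, unchanged baseline kidney disease is counted as something that happened on treatment. In the composite, such patients add events to both arms that carry no information on the capsule. In the safety data, they generate SAE reports and send cases to the Clinical Events Committee when nothing has changed. They may also reach the pooled SAE count used at the blinded interim safety review.

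**Working it through.** The plan gives no figure for this point, so there is none to reproduce. The check sets the definitions side by side and then does simple arithmetic.

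**1. Can an unchanged patient qualify?** Take a baseline eGFR of 40.
- Inclusion item 4.7: 40 < 60, so the patient is eligible on this item. No exclusion sets an eGFR floor.
- Renal composite: 40 < 45, so the eGFR limb is met. If the word persistent carries over from creatinine to eGFR, it does not help, because long-standing kidney disease is persistent.
- SAE list: 40 < 45, so the entry is met on the plain reading with a change of 0%. Adverse events are recorded from Visit 2 and the next kidney test is at Visit 3, so this first arises at week 12.

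**2. How do the two eGFR limbs of the SAE entry relate?** A 30% fall from baseline *b* gives 0.70 × *b*. This equals 45 when *b* = 45/0.70 = 64.3. For any lower baseline, a fall of more than 30% is already below 45, so the relative limb adds nothing. The fall that takes the value down to 45 is (*b* − 45)/*b*:

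| Baseline | Fall to 45 | Value after a 30% fall |
|---|---|---|
| 59.9 | 14.9/59.9 = 24.9% | 41.9 |
| 55 | 10/55 = 18.2% | 38.5 |
| 50 | 5/50 = 10.0% | 35.0 |
| 46 | 1/46 = 2.2% | 32.2 |
| 40 | none needed | 28.0 |

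Everyone enrolled under item 4.7 has a baseline below 60, hence below 64.3. For all of them the absolute limit decides.

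**3. How many patients?** The documents give no baseline eGFR distribution. Assume that 10% to 50% of patients have eGFR below 60, and that 10% to 50% of those are below 45.
- Low end: 0.10 × 0.10 = 1%; 530 × 0.01 = about 5 patients.
- A middle case: 0.30 × 0.25 = 7.5%; 530 × 0.075 = about 40.
- High end: 0.50 × 0.50 = 25%; 530 × 0.25 = about 132.
- Among the 265 patients at the interim review: 265 × 0.01 = about 3, to 265 × 0.25 = about 66.

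**4. Dilution of the composite.** Suppose a share *s* of each arm counts automatically and the remaining patients differ between arms by *d*. The difference over all patients is then (1 − *s*) × *d*. With *s* of 1%, 7.5% and 25%, it is 0.99*d*, 0.925*d* and 0.75*d*.

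**5. Persistence.** A first abnormal value at week 12 can be checked at the scheduled week 26 test. A first abnormal value at week 26 has no later scheduled kidney test.

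**The case against.** **The SAE wording can be read more narrowly.** The word reduction may govern both limbs, meaning a fall by more than 30% or a fall to below 45. A stable low value also has no on-treatment onset to record. This is a fair reading of an ambiguous phrase, and on it an unchanged value is not an event. It does not cure the definition: 46 to 44.9 (1.1/46 = 2.4%) and 40 to 39 (1/40 = 2.5%) would still be SAEs. It does nothing for the renal composite.

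**Details may sit elsewhere.** Handling of prevalent cases is often left to an analysis plan or to adjudication criteria, and the Clinical Events Committee is said to have such criteria. This stands in part for the exploratory composite, where Visit 1 eGFR identifies the patients. It stands less for SAE reporting, which starts with enrolment and cannot be undone later.

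**Other exclusions may remove some of these patients.** Secondary hypertension and solid organ transplantation are excluded. Neither sets an eGFR floor.

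**Stronger readings that the documents do not support:**
- *That many patients are affected.* Item 4.7 is one of seven entry routes and no baseline distribution is given.
- *That baseline disease is automatically booked as drug toxicity and drives the interim decision.* The interim review counts only SAEs judged at least possibly related. Crossing the threshold lets the monitoring committee ask for unblinding; it does not stop the trial.
- *That a first abnormal value at week 26 can never be shown to persist.* The emergency unblinding item of the Safety assessment says that SAEs are followed until they resolve or stabilise, so unscheduled values may exist. What is missing is a scheduled test common to all patients.
- *That the creatinine references contradict each other.* Doubling is measured from the upper limit of normal in the outcome and from baseline in the SAE list. An exploratory outcome and a safety trigger may use different references.

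**Conclusion.** The eligibility rule and the two uses of eGFR below 45 do not fit together as written. It is certain from the text that patients below 45 may be enrolled, that such a patient meets the renal outcome without any change, and that on the plain reading the patient also meets the pre-specified SAE at week 12. It is equally certain that the absolute limit overrides the 30% criterion for every baseline below 64.3.

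The size is not certain. About 5 to 132 of 530 patients follows only from the assumed 1% to 25% entering below 45. Under the same assumption, and with equal shares in both arms, the difference in the renal composite shrinks to between 0.99 and 0.75 of its value in the remaining patients.

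Randomisation should spread these patients evenly, so the main effect on the composite is dilution, not bias. On the safety side the effect is needless reporting and adjudication. The interim threshold is touched only where such SAEs are judged at least possibly related. The renal composite is exploratory, and the primary analysis is not affected. The point should be corrected, but it does not threaten the trial's main result.

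**What to change.** 1. **Renal composite (Pre-specified exploratory outcomes, item 3.1).** Count eGFR below 45 only when it is new since the Visit 1 value, that is, when baseline eGFR was at or above 45. Say whether the persistence requirement applies to the eGFR limb.
2. **SAE list.** Reconcile the Inclusion criteria, the Exclusion criteria and Safety assessment, item 3, so that a value already present at baseline is not reported as an on-treatment SAE. Which eligibility limit or reporting threshold is right is for the sponsor and the clinical team to decide.
3. **Table 1.** Add creatinine and eGFR to the week 52 blood draw, which already serves glucose and lipids, so that a first abnormal value at week 26 has a scheduled later test.

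The cost is wording in the protocol and case report form, and one added assay at an existing draw. Patients who enter below 45 can no longer contribute through the eGFR limb of the composite, but they still can through its other components. Visit 1 eGFR is already collected, so the baseline condition needs no new data.

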Traditional Chinese medicine (TCM) compounds, by virtue of their “multi-component, multi-target, multi-pathway” intervention characteristics, offer novel insights for the comprehensive management of MetS. Meta-analyses have shown that TCM or the combination of TCM and Western medicine can effectively improve metabolic syndrome and reduce cardiovascular and cerebrovascular risk (19–21). Tongmai Jiangtang Capsule (TJC) is an innovative proprietary Chinese medicine developed independently, derived from the classical empirical formula “Method for Boosting Qi, Activating Blood, and Dredging Collaterals.” Its main components include Astragalus membranaceus (Huangqi), Salvia miltiorrhiza (Danshen), Ligusticum chuanxiong (Chuanxiong), Hirudo (Shuizhi), and Pheretima (Dilong), among others. Modern pharmacological studies have confirmed that its core active ingredients (e.g., astragaloside IV, tanshinone IIA, ligustrazine) can ameliorate metabolic disorders through multiple mechanisms (22–26): On one hand, astragaloside IV can activate the AMPK pathway—a key energy sensor that not only enhances insulin sensitivity and inhibits hepatic gluconeogenesis but also exerts anti-inflammatory effects by suppressing NF-*κ*B signaling—thereby ameliorating metabolic disorders; tanshinone IIA can downregulate the expression of inflammatory cytokines (TNF-α, IL-6) in adipose tissue, alleviating IR. On the other hand, ligustrazine and hirudin can inhibit platelet overactivation, reduce hypercoagulability, and simultaneously improve vascular endothelial function and delay the formation of atherosclerotic plaques by modulating the endothelin-1 (ET-1)/nitric oxide (NO) balance. Preliminary studies have indicated that TJC has beneficial effects on both macro- and micro-vascular complications of diabetes, with a good safety profile (27–32); however, its impact on hard cardiovascular and cerebrovascular endpoints (e.g., myocardial infarction, stroke, cardiovascular death) remains unclear.

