## Discussion

Driven by the high prevalence of MetS, its associated elevated cardiovascular and cerebrovascular risk, and the current lack of clarity regarding the effect of Tongmai Jiangtang Capsule—a glucose- and lipid-lowering agent—on cardiovascular events in MetS patients, there is an urgent need to fill the gap in high-level evidence for TCM compounds in this domain, prompting the initiation of this study. The adoption of a multi-center, double-blind RCT design represents the current “gold standard” for validating intervention efficacy. The multi-center design, by enrolling patients from diverse geographical regions (North, East, South, Southwest, Northwest China) and lifestyles (urban/rural), significantly enhances sample representativeness and reduces the “selection bias” inherent in single-center studies. Compared to other TCM studies, the multi-center nature of this trial better aligns with the characteristics of MetS, which involves “multi-system involvement and high population heterogeneity,” thereby strengthening the generalizability of the findings.

Notably, this study sets the primary endpoint as 3P-MACE (including non-fatal myocardial infarction, non-fatal stroke, and cardiovascular death). This “hard endpoint” directly reflects clinical outcomes and holds greater clinical significance compared to surrogate markers commonly used in traditional studies (39) [e.g., carotid intima-media thickness [IMT], flow-mediated dilation [FMD]]. The secondary endpoints encompass metabolic parameters and vascular-related indicators, addressing the developmental cascade of MetS: “metabolism-vascular injury-cardiovascular events.” This “stratified endpoint design” breaks through the limitation of traditional TCM research that often “emphasizes symptoms over hard outcomes,” better aligning with the core requirement of modern evidence-based medicine for demonstrating “clinical value.”

TJC has been marketed for years. Previous clinical trials and observational studies indicate that its adverse reactions are primarily mild gastrointestinal discomfort, with no reports of severe hepatic or renal impairment, ensuring good patient tolerability. Multiple clinical studies suggest that TJC can improve insulin resistance, effectively alleviate diabetic neuropathy and nephropathy, and improve prognosis in diabetic patients with cerebral infarction (32, 40).

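### The one IDMC review described, and its only trigger for a between-arm look, count product-related SAEs only; ischaemic events and non-bleeding deaths judged unrelated fall outside it

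*Protocol article*

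**What the plan says.** All references are to the protocol article.

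- **Safety assessment, item 4** describes a single blinded interim safety review, held once 265 participants have had 12 weeks of treatment. Its content is stated: "The IDMC will review the incidence of SAEs that are possibly, probably, or definitely related to the investigational product".
- The same item gives one route to a between-arm comparison: "If the pooled incidence of drug-related SAEs exceeds a pre-defined safety threshold", the IDMC may ask for allocation. The threshold is to come from past experience with TJC and comparable herbal products.
- **Safety assessment, item 1** has every AE recorded in the CRF, related or not.
- **Safety assessment, item 2** sends the outcome events elsewhere: "The CEC will adjudicate all suspected cardiovascular and cerebrovascular endpoints (including 3P-MACE) and all serious adverse events (SAEs) in a blinded manner". No route from that committee (CEC) to the IDMC is described.
- **Safety assessment, item 3** pre-specifies bleeding, coagulation and platelet, liver and renal events as SAEs needing immediate reporting and adjudication. It does not name the IDMC as recipient.
- **Safety assessment, item 5** has individual emergency unblindings "reported to the IRB and IDMC within 24 h".
- **Introduction**, on what is known of TJC: "its impact on hard cardiovascular and cerebrovascular endpoints (e.g., myocardial infarction, stroke, cardiovascular death) remains unclear". **Discussion**, on past experience: "its adverse reactions are primarily mild gastrointestinal discomfort".
- All-cause mortality appears under the pre-specified exploratory outcomes only.

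**The concern.** In a cardiovascular outcome trial the gravest harm to look for is more infarctions, strokes or deaths on active treatment. These are also the events for which individual causality judgement works worst. Inclusion requires age 65 or over and established vascular, cardiac or renal disease, so almost any ischaemic event has a ready explanation in the patient's history. The article reports mainly gastrointestinal reactions to TJC, which gives an assessor little reason to call an infarction drug-related. Comparing randomised arms needs no such judgement, but item 4 applies it twice: once to decide which events the IDMC counts, and again to decide whether it may ask for allocation. Followed as written, the review could pass over an excess of MACE or deaths that the CEC had already adjudicated.

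**Working it through.** **1. Which events reach the review, reading the items together**

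| Event | Adjudicated by CEC (item 2) | Counted in the IDMC review (item 4) |
|---|---|---|
| SAE judged at least possibly related | yes | yes |
| Bleeding, coagulation, liver or renal event listed in item 3 | yes | if judged related; the item's title ties these to TJC components |
| Ischaemic MACE judged unrelated | yes | no |
| Non-bleeding death judged unrelated | yes | no |
| Emergency-unblinded case | yes, if an SAE | notified singly (item 5), not as an incidence |

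**2. The plan's own figure.** 530 × 0.50 = 265, as stated for the timing of the review.

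**3. Size, as an illustration only.** From the article: 530 participants, recruitment over 3 years, 52 weeks per participant, and a 10-year event risk above 40% in MetS with diabetes. Assumed: uniform accrual, no dropout, that risk used as the control hazard, MACE doubled on TJC for 52 weeks or for the 26 treatment weeks only, and the same share judged related in both arms.

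- Accrual: 530/36 = 14.7 per month. The 265th participant enters at month 18; adding 12 weeks gives month 20.8, with about 306 randomised.
- Control hazard: −ln(0.6)/10 = 0.0511 per year.
- Expected first MACE per arm: the integral of 1 − exp(−H(t)) over accrual, with follow-up capped at 12 months. Placebo 5.43. As a rough check, 217.3/2 patient-years × 0.0511 = 5.55, slightly above the first-event count. TJC 10.62 (52-week harm) or 8.60 (26-week harm).
- Pooled: 5.43 + 10.62 = 16.05, or 5.43 + 8.60 = 14.03.
- Left out if half are judged related: 16.05 × 0.5 = 8.0, or 14.03 × 0.5 = 7.0. At 75% related: 4.0 or 3.5. At 25%: 12.0 or 10.5. Haemorrhagic events already counted would lower these.

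**4. Gain in detection, keeping the plan's pooled-first sequence.** Assumed trigger: the smallest pooled count with a Poisson tail of at most 10% under no effect. Then an exact conditional binomial comparison at one-sided 10%.

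| Scope | Trigger count | Trigger then flag, 52-week harm | Trigger then flag, 26-week harm |
|---|---|---|---|
| All MACE | 16 | 24.5% | 9.2% |
| 75% judged related | 13 | 16.9% | 6.4% |
| 50% judged related | 9 | 13.3% | 5.9% |
| 25% judged related | 6 | 3.7% | 1.5% |

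- Excess MACE still to come after the review: 12.5 − 5.2 = 7.3 (52-week harm) or about 3.2 (26-week harm).
- Incremental avoidable excess at 50% related, if the trial stopped at once: 7.3 × (0.245 − 0.133) = 0.8, or 3.2 × (0.092 − 0.059) = 0.1.
- At hazard ratio 1.5 the all-MACE sequence flags only 6% or 3%.
- Over control hazards of 3% to 10% per year, the all-MACE flag runs from 12% to 45% (52-week harm) or 5% to 18% (26-week harm).

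**5. Sensitivity to the trigger.** At 50% related the tail at a count of 9 is 0.0997, barely inside the 10% rule. A trigger of 10 lowers the 52-week flag from 13% to 9%. A trigger of 5 raises the flag to 22% (52-week) or 12% (26-week), with more false triggers. The article gives no threshold value, so none of these is the plan's own performance.

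**The case against.** The strongest reply is that item 4 says what the IDMC will review at one look and never says that it reviews nothing else. The committee includes a cardiovascular specialist, a neurologist and a biostatistician, and its full remit would normally sit in a charter that a journal article does not reproduce. A reader might infer that the IDMC is barred from seeing MACE and deaths, or that nobody watches them. The documents do not support that: the CEC adjudicates them all, a charter may widen the scope, and any event judged even possibly related is counted. What stands is that item 4 states a narrow content and a narrow trigger. If the charter is wider, item 4 misdescribes it.

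The gap is also smaller than it first looks. Possible relatedness is a low bar, the article does not say who applies it, and item 3 picks out the bleeding, coagulation, liver and renal events most plausibly linked to the product. This is right, and it confines the point mainly to ischaemic events and non-bleeding deaths.

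A reader might further infer that the wider scope would reliably catch harm. It would not. There are few events by the review, the modelled gain depends on an assumed trigger, and with a low enough trigger the related-only count does about as well as the all-MACE count at its own trigger. Those figures show scale only.

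Finally, routine by-arm tables would turn a deliberately blinded review into a comparative look at the primary endpoint. That is a legitimate choice either way and is not needed to close the gap.

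**Conclusion.** The point holds as a matter of stated scope. The one IDMC review described, and its only stated trigger for a between-arm look, depend on attribution to the product, in a trial where the events of most concern are those that attribution handles worst. It is worth correcting because it bears on participant safety and is cheap to put right.

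The size is modest. Under an assumed 5.1% per year control hazard, uniform accrual and doubled MACE, about 14 to 16 first MACE occur by the review, and 7 to 8 are left out if half are judged related. Counting them raises the chance of a flag from about 13% to 25%, or from 6% to 9% if harm is confined to treatment. That is worth at most about 0.8 or 0.1 avoidable events, and moderate harm would usually be missed under either scope. Confidence is medium because the charter, the threshold and the share of events judged related are not shown. The case for the change rests on the wording of item 4 rather than on these figures.

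**What to change.** Reword Safety assessment, item 4 so that the existing review covers all-cause death, CEC-adjudicated 3P-MACE and all SAEs regardless of relatedness, with the related-SAE count kept as an additional line. State that the IDMC may request by-arm data on any of these, for harm only, without the related-SAE threshold first being crossed. State that there is no stopping for benefit, so the final alpha is unchanged. Routine by-arm display in closed session is optional. If the charter already provides this, item 4 should say so.

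Cost: one extra table of events that the CEC already adjudicates, with no new visits, participants or committee. The downsides are that the IDMC learns allocation if it asks, and a small chance of a false harm alarm. In the illustration that chance is about 0.5% if a pooled trigger comes first and about 6% with a direct by-arm look.

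### APTT/PT prolongation is a pre-specified SAE, but no listed or scheduled laboratory test measures it

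*Protocol article*

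**What the plan says.** All references are to the Protocol article.

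- **Pre-specified SAEs (Safety assessment, item 3).** Citing the Hirudo component, the article lists events to be reported at once and adjudicated. The laboratory criteria are "prolongation of APTT or PT > 1.5× upper limit of normal (ULN"), "platelet count < 50 × 10⁹/L", ALT or AST above three times ULN, a fall in eGFR or a low eGFR, and doubling of creatinine. Several kinds of clinical bleeding are listed separately.
- **Laboratory list (Safety assessment, item 1).** "Laboratory tests include complete blood count, urinalysis, blood biochemistry, and 12-lead ECG". Biochemistry is then itemised: "Blood biochemistry will specifically include alanine aminotransferase (ALT), aspartate aminotransferase (AST), albumin (ALB), creatinine (Cr), blood urea nitrogen (BUN") and eGFR.
- **Schedule (Table 1).** The safety laboratory rows are "Blood routine, Urine routine, Fecal routine" and "Liver function(ALT, AST, ALB), kidney function(UN, Cr, UA, eGFR"), each marked at baseline, Week 12 and Week 26.
- **Interim review (Safety assessment, item 4).** When 265 participants have completed 12 weeks, the IDMC reviews SAEs "related to the investigational product, without being unblinded to treatment assignment". It may ask for group assignments under one stated condition: "If the pooled incidence of drug-related SAEs exceeds a pre-defined safety threshold (based on historical data of TJC and similar herbal products").

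**The concern.** An event definition that depends on a laboratory value needs that value to be obtained in the same way in both arms. Here the criterion tied most directly to the article's stated reason for the list, the Hirudo component, has no measurement behind it. Whether a prolonged APTT or PT is found would depend on whether someone ordered the test for another reason. Testing of that kind tends to follow symptoms, procedures or co-medication, and its frequency may differ by site and by arm.

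Two things are at stake. A low count of this SAE at the end of the trial could not be read as evidence of no effect on coagulation. And where a prolonged value is found, there would be no scheduled baseline with which to judge whether it was already present, in a population aged 65 or over whose standard care may include aspirin.

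**Working it through.** **1. Each laboratory SAE against the tests that could detect it**

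| Laboratory SAE (item 3) | In the item 1 list? | In Table 1? | Baseline value scheduled? |
|---|---|---|---|
| APTT or PT | No | No | No |
| Platelet count | Yes, blood count | Yes, blood routine | Yes |
| ALT or AST | Yes | Yes, liver function | Yes |
| eGFR | Yes | Yes, kidney function | Yes |
| Creatinine | Yes | Yes, kidney function | Yes |

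Four of the five rows are covered at baseline, Week 12 and Week 26. APTT/PT is the only one with no test at any visit. Table 1 is detailed enough to list fecal routine, vitamin D, UACR and BNP as separate entries, and none of its rows is a coagulation test.

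**2. The interim review (background to the optional suggestion)**

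The one stated figure reproduces: 0.5 × 530 = 265.

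The article gives no SAE rate and no threshold, so everything below rests on assumptions: 133 TJC and 132 placebo participants, with related-SAE rates of 4% and 1%.

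- Expected events: 133 × 0.04 + 132 × 0.01 = 5.32 + 1.32 = 6.64. Pooled rate: 6.64 / 265 = 2.5%.
- With no difference (2.5% in each arm), expected events are 265 × 0.025 = 6.63, and the pooled rate is again 2.5%.

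The chance of crossing a pooled threshold is the upper tail of the sum of two independent binomial counts:

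| Assumed threshold | Events needed of 265 | 4% vs 1% | 2.5% vs 2.5% | 1% vs 1% |
|---|---|---|---|---|
| >1.5% | 4 | 0.90 | 0.90 | 0.27 |
| >2% | 6 | 0.65 | 0.65 | 0.05 |
| >3% | 8 | 0.35 | 0.34 | 0.006 |
| >5% | 14 | 0.007 | 0.007 | <0.001 |

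The fourth and third columns are almost identical, so the pooled count cannot tell a fourfold excess from no excess at the same overall rate. The last column shows that a trigger can still work if the background rate really is known to be 1%: >2% is crossed with probability 0.65 under the excess, against 0.05 false flags. For comparison, a one-sided 5% Fisher test on the unblinded arms would be significant with probability 0.29 at 4% vs 1%.

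**The case against.** **On the coagulation test.** The wording that introduces the laboratory list is not closed, and a journal article may drop a row that the full protocol holds. That is fair and limits how far the point goes. It does not remove it, because the article itemises the biochemistry and prints a detailed schedule, and every other laboratory SAE can be traced to both. It is also one criterion among many.

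**A stronger reading that the article does not support.** A reader might infer that bleeding surveillance as a whole cannot work. It can. Clinical bleeding is itself a pre-specified SAE and needs no APTT or PT. All AEs are recorded whether or not judged related, platelets are scheduled, the Clinical Events Committee adjudicates all SAEs blinded, and emergency unblindings are reported to the IDMC within 24 hours. Bleeding can be compared by arm at the end.

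**On the interim review.** A reader might also infer that the IDMC can never see the arms, or that pooling hides an excess. The first is wrong, since item 4 allows group assignments to be requested once the threshold is crossed. The second is too strong. Pooling dilutes an excess, but a trigger calibrated to a correctly known background can flag a large one, and under the rates assumed here it does so more often than a Fisher test by arm (0.65 against 0.29). A blinded first look with conditional unblinding is a deliberate design, and the threshold value may sit in an IDMC charter. What stands is narrower: the trigger depends on a historical rate being right for this population and this SAE list, which a by-arm comparison does not need.

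**Conclusion.** The inconsistency holds and is narrow. One of the pre-specified laboratory SAEs, APTT/PT prolongation, has no listed or scheduled test and no scheduled baseline, while all the others do. Followed as written, its incidence in each arm would be incomplete and hard to interpret. How many events would be missed cannot be computed, because the article gives neither an expected rate nor a frequency of unscheduled testing. The conclusion assumes that the article's list and schedule reflect the full protocol.

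The interim review is not an error. Its figures depend on rates and thresholds that the article does not state, so that part stands only as a suggestion.

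**What to change.** Reconcile item 3 of the Safety assessment with item 1 and Table 1, so that every pre-specified laboratory SAE is either measured in both arms at the existing baseline and treatment-phase blood draws, or removed from the list. If the criterion is kept, the cost is one coagulation tube at draws already scheduled, plus a line in the laboratory list and a row in Table 1. If it is removed, the cost is a wording change. If the full protocol already schedules the test, correcting the article is enough.

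Optional: at the planned review, an unblinded statistician outside the trial team could give the IDMC closed tables by arm of all SAEs and all bleeding events, whatever the attributed relatedness, with trial staff kept blind. No efficacy comparison is made, so no alpha is spent. The cost is charter wording and one closed report.
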